## Discussion

To the best of our current knowledge, this is the first randomized, double-blind, and placebo-controlled trial assessing the role of *L. plantarum* 299v in the prevention of weight loss, improvement of nutritional status, EN tolerance, and QOL of cancer patients receiving HEN.

The beneficial effects of *L. plantarum* 299v for several diseases have been demonstrated in many clinical trials [14, 16]. Hoppe et al. reported that administration of *L. plantarum* 299v increases iron absorption in women [17]. Additionally, as it was stated above, *L. plantarum* 299v is effective in supporting treatment of IBS. Moreover, in Dudzicz et al. study, it was confirmed that routine use of *L. plantarum* 299v may prevent *Clostridium difficile* infection (CDI) during antibiotic therapy in patients receiving immunosuppressing agents and being hospitalized in nephrology and transplantation ward [18]. Furthermore, the results of Wullt et al. study, indicated that *L. plantarum* 299v reduces the side effects of antibiotics on colonic fermentation in patients suffering from recurrent *Clostridium difficile*-associated diarrhoea [19]. The significant reduction of antibiotic-associated gastrointestinal symptoms (the frequency of loose stools and nausea) after administration of *L. plantarum* 299v has been confirmed in a double-blind and placebo-controlled Lönnermark et al. trial [20].

EN provides many benefits for cancer patients, mainly preventing mucosal atrophy, reducing endotoxins translocation, and preserving gut immunity; however, as it was stated above, it is associated with adverse events, while the most common one is diarrhoea [2, 21]. The incidence of diarrhoea is increased in critically ill patients [22]. Probiotic strains may be used to prevent side effects of EN which was shown in Zhao et al. study [23]. This trial recruited 120 patients with gastric cancer receiving EN in combination with probiotics for 7 days after the surgical procedure. The patients were divided into 3 groups: first received fiber-free nutrition formula (*n* = 40), second consumed fiber-enriched nutrition formula (n = 40), and third received fiber- and probiotics-enriched nutrition formula (n = 40). Patients receiving probiotics-enriched nutrition formula had a lower risk of developing diarrhoea. However, the laboratory parameters assessing nutritional status did not differ significantly between groups [20]. The similar results were obtained by Xie et al. [24]. In this study including 140 patients with gastric cancer receiving EN and probiotics for 8 days, the decrease in the incidence of diarrhoea and reduction of the pro-inflammatory cytokines level (IL-6, IL-8, and TNF-α) in the postoperative period were reported. However, the laboratory parameters assessing nutritional status did not change [22]. Overall, the results of these above mentioned studies confirm that probiotic strains are effective in reducing the occurrence of diarrhoea. Notwithstanding, due to short period of administration of EN and probiotics (7 and 8 days), it was difficult or almost impossible to improve the nutritional status of cancer patients.

In our study, we decided to administer the probiotic strain *L. plantarum* 299v in full dose (2 × 10^10^ CFU) for 12 weeks, which allows us to expect changes in anthropometric and laboratory parameters (especially in cases of parameters with a long half-life, for instance in case of albumin). The possibility of *L. plantarum* 299v to reduction of gastrointestinal symptoms related to EN may contribute to improvement of EN tolerance and as a consequence to improve patients’ QOL.

There may be some possible limitations in the design of the study:
First, this is a single centre study with small sample size; moreover, the group is non-homogenous. It could take a lot of time to recruit more patients and with the same type of cancer, due to high mortality of cancer patients qualified for HEN. Additionally, not every patients fulfilling inclusion criteria is able to take part in this study. Therefore, there is a need to create a multi-center study to have a better chance for a larger sample size.Second, the participants will intake the capsules at home, so we cannot be completely certain if they will really administer the intervention products.Third, the tolerance of enteral nutrition will be assessed by questionnaire fulfilled by patients at home, thus we cannot be sure if they will do it every day or simply before follow-up visits.

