### Data collection

#### Participant timeline

The timetable of follow-up visits and measurements is presented using The Standard Protocol Items: Recommendations for Interventional Trials (SPIRIT) diagram in the Table 1. Each of the participants will visit the study centre three times (at baseline, after 4 weeks, and after 12 weeks). During follow-up visits, patients will receive study products depending on allocation. At baseline – 60 capsules for 30 days; after 4 weeks – 120 capsules for next 60 days. If during this trial, any participant fails to continue the study protocol, the data will be collected and this information will be further noted in the publication.

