### Statistical analysis

When computing a priori sample size, we assummed that of all existing approaches used in screening and assessment of malnutrition and cachexia, weight loss – among others - is a phenotype always evaluated by international organizations and commonly used tools/surveys [15], that this parameter will serve as pivotal to calculate required sample size. Calculating the mean weight loss (major component of nutritional status) in a 70 kg men and assuming 1:1 allocation ratio and 80% statistical power we evaluated that the number of participants will be 36. Allowing for a withdrawal rate of 20% for the primary outcome we aim to randomly allocate 40 participants to receive either active product or placebo. The required sample size were evaluated using G-power analysis software. Significance level will be 0.05.

The calculations will be carried out with the use of Statistica package by Dell Inc. The descriptive statistics will include averages, medians, standard deviations, maximum and minimum values. In order to check the normality of distribution of populations subject to research, the W Shapiro-Wilk test will be applied. To check the homogeneity of variations of the groups compared, the Brown-Forsythe test will be applied. Then, depending on the type of data and shape of distributions compared, the U Mann-Whitney test, Student’s t-test or a version of Student’s t-test with independent variance estimation will be applied.

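### The plan allows for 20% withdrawal in a population it calls high-mortality, but its stated tests have no place for death or a missing weight, so the primary comparison defaults to patients with a follow-up weight

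*Protocol article*

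**What the plan says.** All references are to the protocol article; no SAP is at hand.

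- **Primary outcome.** Prevention of weight loss, probiotic against placebo. No time point is named and death is not mentioned.
- **Study design; Participant timeline.** Assessments are at weeks 0, 4 and 12, at three visits to the centre. No weighing away from the centre is described.
- **Participant timeline.** If, during the trial, "any participant fails to continue the study protocol, the data will be collected and this information will be further noted in the publication".
- **Statistical analysis, sample size.** The required number is derived "assuming 1:1 allocation ratio and 80% statistical power", and "the number of participants will be 36". Then: "Allowing for a withdrawal rate of 20% for the primary outcome we aim to randomly allocate 40 participants".
- **Statistical analysis, tests.** Student's t-test, its separate-variance version, or Mann-Whitney, chosen by data type and distribution. No covariate, repeated-measures analysis or rule for missing values is stated.
- **Discussion, limitations.** Enlarging the sample with a single cancer type would be slow "due to high mortality of cancer patients qualified for HEN". The other limitations concern the single centre, mixed diagnoses, capsule adherence and diary completion. Loss to follow-up is not among them.

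**The concern.** Withdrawal appears in the plan only as a headcount. The phrase "Allowing for a withdrawal rate of 20% for the primary outcome" implies that about a fifth of patients will have no primary outcome, and the response is to recruit more. That protects precision but not validity.

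In this population, absence of a weight is unlikely to be unrelated to weight. The Background reports that almost three quarters of patients qualified for home enteral nutrition are malnourished and that about half of patients with malignancies develop cachexia. Patients who die or become too ill to travel are plausibly those losing most weight. A two-sample test on observed weights leaves them out.

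At stake is the meaning of the result. If more wasted patients are lost from one arm, that arm looks better than it is. A product that kept frail patients in follow-up would be penalised for doing so. The listed tests also make no use of the baseline and week-4 weights of patients who have no week-12 weight, if week 12 is the comparison made.

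**Working it through.** **Inputs from the document.** Significance level 0.05 (sidedness not stated; two-sided taken here), 80% power, 1:1 allocation, 36 required, 20% withdrawal, 40 randomised. The basis is "Calculating the mean weight loss (major component of nutritional status) in a 70 kg men", with no difference in kg and no SD.

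**Step 1. The plan's own figures.** The 36 cannot be rebuilt without a difference and an SD. Solving the two-sample t-test backwards for 18 per arm gives a standardised effect of d = 0.96 (0.85 if one-sided). The 40 does not follow from 36 and 20%: 36 / (1 − 0.20) = 45. At 20% loss, 40 × 0.80 = 32 patients remain, 16 per arm, and power at d = 0.96 is about 75%. That mismatch is a separate point. It is used here only for scale.

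**Step 2. Shift in one arm.** These assumptions are not in the document. Standardised weight change is normal, with higher values meaning less loss. It has correlation ρ with general condition, and the fraction p in worst condition is lost. Among those who remain, the mean is overstated by

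shift(p) = ρ × φ(z_p) / (1 − p),

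where φ is the standard normal density and z_p its p-quantile.

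- p = 0.20: 0.2800 / 0.80 = 0.350, so the shift is 0.105, 0.175 and 0.245 SD for ρ = 0.3, 0.5 and 0.7.
- p = 0.30: 0.3477 / 0.70 = 0.497.
- p = 0.10: 0.1755 / 0.90 = 0.195.

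**Step 3. Shift in the treatment difference, no true effect.**

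- Equal loss (20% in each arm, same mechanism): the shifts cancel and the difference is unbiased.
- 30% against 10% (20% overall): ρ × (0.497 − 0.195) = ρ × 0.302, which is 0.09, 0.15 and 0.21 SD, in favour of the arm that loses more. Relative to d = 0.96 this is 9%, 16% and 22%.

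**Step 4. A second loss model.** Here loss depends directly on weight change. The odds of loss are multiplied by 1.65 to 4.5 for each SD of worse change, with average loss 20%; results are by simulation.

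| Loss, probiotic v placebo | Bias in the difference (no true effect) |
|---|---|
| 20% v 20% | about 0 |
| 15% v 25% | 0.05 to 0.10 SD against probiotic |
| 10% v 30% | 0.09 to 0.21 SD against probiotic |
| 5% v 35% | 0.14 to 0.31 SD against probiotic |

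With a true effect of 0.96 SD and the same loss mechanism in both arms, the better arm keeps more patients. The estimate among those weighed is then 0.79 to 0.93 SD, or 82% to 96% of the truth.

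**Step 5. Against sampling error.** With 10% and 30% lost from 20 per arm, 18 and 14 remain. The standard error of the difference is √(1/18 + 1/14) = 0.36 SD, so a bias of 0.09 to 0.21 SD is roughly a quarter to three fifths of it.

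**The case against.** The strongest reply is that this criticises silence. Analysis sets, missing-data rules and the treatment of death commonly sit in a full protocol or SAP, neither of which is shown. The named tests do not in themselves exclude anyone: a t-test can follow imputation, and Mann-Whitney can take worst ranks for deaths. The trial is double-blind, and nothing in the article predicts unequal loss. With equal loss and no effect the difference is unbiased, and even the assumed bias is smaller than one standard error.

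Much of this stands, and it rules out several stronger readings that a reader might infer:

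- *That the primary test is at week 12.* No time point is named, and weight is also taken at week 4.
- *That the plan restricts the analysis to survivors or observed cases.* No sentence says so. It is the default result of the listed tests, not a written rule.
- *That non-completers are merely mentioned in the report.* The article says that their data will be collected, so patients who stop capsules but survive may still be weighed. It does not say that those weights will be analysed.
- *That the plan forecasts high mortality within the trial.* The remark explains slow recruitment and gives no rate, though it describes the population from which patients are drawn.
- *That being unable to visit the centre removes patients during follow-up.* It is an entry criterion.

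What the reply does not remove is the choice that is written down: unadjusted two-sample tests, with loss covered by headcount alone. A baseline-adjusted or repeated-measures analysis in a later SAP would be a change from the stated methods, not a detail filled in.

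**Conclusion.** The point holds in limited form. The plan expects withdrawals that affect the primary outcome, in a population it describes as high-mortality, and states only tests that cannot use a patient without a follow-up weight. The comparison therefore defaults to patients who could be weighed. It would go too far to say that the primary answer is a survivors' comparison or that it will be biased.

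The bias in the treatment difference is about zero if loss is equal and there is no true effect. It is about 0.09 to 0.21 SD if loss is 30% against 10% and frailty correlates 0.3 to 0.7 with weight change. The second model, over a wider range of imbalance, gives about 0.05 to 0.31 SD. All of these rest on assumed correlations and loss rates, and d = 0.96 is back-solved. The change is inexpensive and should be made, but the omission does not by itself invalidate the design.

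**What to change.** In the Statistical analysis section:

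1. Name the primary time point, for example week 12.
2. Analyse all randomised patients in their allocated arm. Use a repeated-measures model of weight change at weeks 4 and 12, with baseline weight, arm, visit and arm-by-visit, so that patients lost after week 4 still contribute.
3. State that weights collected after capsules are stopped, which Participant timeline already foresees, are included.
4. Add two sensitivity analyses: a rank analysis with death before the primary time point as the worst outcome, and a delta-adjusted analysis for other missing weights.
5. Report deaths and missing weights by arm and visit.

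The cost is revised wording and some programming; no visits or measurements are added. The main model assumes that weights are missing at random and, in effect, assigns a weight trajectory to patients who have died. Patients lost before week 4 add nothing to a model of change. The sensitivity analyses are there to probe these limits, so they should be specified in advance together with the main model.

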## Data Availability

It is only a study protocol, so the data are not available yet.

## Abbreviations

HEN: home enteral nutrition
EN: enteral nutrition
*L. plantarum* 299v: *Lactobacillus plantarum* 299v
OQL: quality of life
NRS 2002: Nutritional Risk Screening 2002 tool
WHOQOL-BREF: World Health Organization Quality of Life-BREF
CDI: *Clostridium difficile* infection
